### 2.11. Outcome Measures

A multiple method of data collection will be used to examine both the statistical and clinical significance level of the intervention and the effectiveness of the intervention.

#### 2.11.1. Primary Outcome

The primary outcome is self-determination of participants with ID. Participants with ID will complete the AIR Self-Determination Scale: The Chinese Version (AIR SDS-C) [32] that is composed of two parts. Part one is a 24-item, 5-point Likert-scale questionnaire to measure self-determination in people with ID, consisting of scores from four domains including self-determination competencies, feelings, school and workplace opportunities and home or hostel opportunities. Higher scores denote higher levels of SD competency. Confirmatory factor analysis (CFA) has revealed a very similar factor structure to the original English version; all the factor loadings were between 0.42 and 0.76, and all items were thus retained. The results of the CFA suggested a relatively good fit to the data (χ2(df = 247, *n* =356) = 392.00, χ2/df = 1.59, RMSEA = 0.041, 90% CI [0.033–0.048], CFI = 0.933, TLI = 0.926, SRMR = 0.05). The Cronbach’s alpha (α) value for the entire scale was 0.88 [32].

#### 2.11.2. Secondary Outcome

The secondary outcome is the personal well-being of participants with ID. Participants with ID will complete the Personal Well-Being: Intellectual Disability (Cantonese) 3rd Edition (PWI-C) that was translated from the Personal Well-being Index developed by Cummins in 1996; Cummins and Lau validated the Cantonese version [67]. The index uses an 8-item, 5-point Likert-scale questionnaire to measure the subjective well-being of people with ID; higher scores indicate better personal well-being. The Kaiser–Meyer–Olkin (KMO) values were >0.80 and the Bartlett’s test also reached statistical significance (*p* < 0.05); the Cronbach α coefficients were 0.80 [68].

#### 2.11.3. Process Outcome

A Self-Determination Action Plan will be developed by the principal investigator and research team. The measure of its effectiveness, using the vignettes method, will examine to what extent the participants with ID in the intervention group can transfer their learning into daily life. The participants will be given several scenarios and will then be required to say what their personal goal is and how they will achieve it; for example, questions such as “give an example of a goal you are working on” or “what are you doing to reach this goal?” will be asked. Self-determination skills, including goal setting, choice making, problem solving and decision making, will be tested. A marking scheme will be developed to quantify the behavioral changes in the participants.

#### 2.11.4. Parents’ Outcomes

A questionnaire will be developed by the principal investigator and research team to measure the perceived changes of the parent participants in the SD-PLUS group in regard to their beliefs, perceptions and skills related to self-determination after the intervention. The questionnaire consists of five items measured on a 5-point Likert-scale. For example, questions such as “I do more agree that self-determination is important to my child with ID” and “I grasped the REACH skills and apply them to support the self-determination of my child with ID” will be asked.

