This study aims to evaluate the effectiveness of the intervention. There are three intervention conditions: (1) SD group—only attended by participants with ID; (2) SD-PLUS group—in the form of a parallel group structure, in which the participants’ caregivers will attend the caregivers’ group; and (3) leisure group—only attended by participants with ID. The hypotheses for the study are as follows:(1)Participants in the SD group and the SD-PLUS group, in comparison with participants in the leisure group, will enhance their self-determination competencies and personal well-being during the post-intervention phase (T1);(2)Participants in the SD group and the SD-PLUS group, in comparison with participants in the leisure group, will enhance their self-determination competencies and personal well-being at the three-month follow-up (T2);(3)Participants in the SD-PLUS group, in comparison with participants in the SD group, will exhibit additional enhancements in their self-determination competencies and personal well-being during the post-intervention phase (T1);(4)Participants in the SD-PLUS group, in comparison with participants in the SD group, will exhibit additional enhancements in their self-determination competencies and personal well-being at the three-month follow-up (T2);(5)Parent participants in the SD-PLUS group will enhance their beliefs, perceptions and skills in regard to supporting their children in exercising self-determination during the post-intervention phase (T1) and at the three-month follow-up (T2).

It will be a challenge for participants recruitment if three intervention conditions are required. However, since this kind of program has never been tried and tested in Hong Kong, the grant’s vetting reviewers suggested to test the program with three conditions.

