#### 2.4.2. Recruitment of Participants

The participants with ID and their caregivers for all arms of the study will be recruited from five non-governmental organizations (NGOs) that provide adult services for people with ID. To achieve diversity in the study samples, the NGOs joining the present study are located in different districts in Hong Kong and currently provide diverse services include community support services, vocational training, employment services and residential services for adults with mild ID. Service users in residential settings have weekly home leaves and they would keep communications and interactions with their families. In addition, service providers reflect that they prefer open recruitment across different settings to recruitment from the same setting. Therefore, no specific service setting is excluded from recruitment. The social workers of the individual organizations will recruit eligible participants and their caregivers based on the inclusion and exclusion criteria for the study. It is known that offering an incentive (e.g., shopping vouchers) to participants upon completion of study is increasingly seen as good practice internationally. However, this study is not able to offer the incentives for the participants since the grant’s budget did not cover this item. Alternatively, the research team is producing additional promotional material (i.e., videos) to facilitate better recruitment. Using lively scenarios and layman language, the videos highlight that participants may benefit from the group intervention itself and their potential contributions to the service development.

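### Hypothesis 5 claims enhancement in SD-PLUS caregivers at T1 and T2, but the only caregiver measure described is perceived change after the course, which gives no T0 level to improve from

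*Protocol article*

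**What the plan says.** **The hypothesis.** Section 2.1 of the protocol article, hypothesis 5, reads "Parent participants in the SD-PLUS group will enhance their beliefs, perceptions and skills in regard to supporting their children in exercising self-determination", and it sets two time points: "during the post-intervention phase (T1) and at the three-month follow-up (T2"). Hypotheses 1 to 4 each name a comparison arm. Hypothesis 5 names none.

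**The measure.** Section 2.11.4 describes one caregiver instrument, which the research team will develop. Its purpose is "to measure the perceived changes of the parent participants in the SD-PLUS group in regard to their beliefs, perceptions and skills", and the sentence ends by placing this after the intervention: "beliefs, perceptions and skills related to self-determination after the intervention". On format, "The questionnaire consists of five items measured on a 5-point Likert-scale". Two items are given as examples. The first concerns belief: "I do more agree that self-determination is important to my child with ID". The second concerns what the course teaches: "I grasped the REACH skills and apply them to support the self-determination of my child with ID".

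**Who is available.** Under Section 2.4.2, "The participants with ID and their caregivers for all arms of the study will be recruited from five non-governmental organizations". Section 2.1 says that caregivers are randomised with the participants into the three arms, and that only the SD-PLUS arm involves caregivers in the intervention.

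**Schedule and analysis.** Section 2.7 has the baseline scales repeated at T1 and T2 and refers to Section 2.11 as a whole, without naming the caregiver form. Section 2.12 relies on hierarchical linear modelling with a time-by-treatment interaction. Its baseline comparison is confined to the participants with ID.

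**The concern.** Enhancement means that a later level exceeds an earlier one. The questionnaire as described asks caregivers, once the course is over, whether they think they have changed. That is a different quantity, and it supplies no earlier level.

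The respondents know which arm they are in, have attended the caregiver sessions, and are asked to agree with statements that describe the course as having worked. A favourable mean could come from a real shift in beliefs and skills, from courtesy, or from a general tendency to agree, and the score cannot separate these.

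What is at stake is one of the five numbered hypotheses. The risk is that agreement with such items is reported as evidence that caregivers improved.

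**Working it through.** The protocol gives no figure for this outcome, so there is none to reproduce. The check sets the sections side by side. A short calculation then shows how little a significant result would mean.

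**1. What hypothesis 5 needs.** A level of belief, perception and skill before the course, and the same level at T1 and at T2.

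**2. What Section 2.11.4 supplies.** A perceived-change score in SD-PLUS caregivers.
- The first example item is comparative. Before the course there is nothing for *more* to refer to. At T2 it is unclear whether *more* means since T0 or since T1, so a T1-to-T2 difference does not measure maintenance or growth of a level.
- The second example item asks about skills taught only in the course. It cannot be answered meaningfully at T0, nor by caregivers who were not taught REACH.

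**3. Whether Section 2.7 closes the gap.** If its general schedule does not extend to the caregiver form, there is no T0 value. If it does, caregivers would be asked before the course how the course had changed them, and Sections 2.7 and 2.11.4 would conflict. Neither reading yields a usable T0 level.

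**4. Whether Section 2.12 can be applied.** A time-by-treatment interaction needs repeated measurement and more than one condition. A post-course score in a single arm offers no second condition and no baseline.

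**5. Illustration of agreement bias.** The available test would compare the mean perceived-change score with the neutral midpoint of the scale.

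Inputs:
- n = 120/3 = 40 SD-PLUS caregivers, from the target in Section 2.3, assuming equal allocation and one caregiver per participant.
- n = 40 × 0.85 = 34 after the 15% drop-out assumed there.
- True change is zero.
- Agreement shifts the mean by b standard deviations above the midpoint. The documents give no value for b, so a range is shown.

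Method: one-sample t test, two-sided α = 0.05, noncentrality b√n.

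| Shift b (SD) | b√40 | Significant, n = 40 | b√34 | Significant, n = 34 |
|---|---|---|---|---|
| 0.2 | 1.26 | 23% | 1.17 | 20% |
| 0.3 | 1.90 | 46% | 1.75 | 40% |
| 0.5 | 3.16 | 87% | 2.92 | 81% |

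An unbiased test would be significant 5% of the time here. A moderate tendency to agree is enough to produce a positive result with no true change.

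**6. Precision if all arms were measured.** This describes a possible remedy, not the size of the defect. Section 2.3 plans five groups of 6–8 per arm, i.e. 30–40 people. For SD-PLUS against the other two arms combined, the standard error of a standardised difference is √(1/40 + 1/80) = 0.19 at the upper end and √(1/30 + 1/60) = 0.22 at the lower end, before clustering, loss and adjustment for T0.

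**The case against.** **The hypothesis can still be tested in some form.** A reader might infer that hypothesis 5 cannot be tested at all because there is no control arm. The text does not support that. The hypothesis is a within-arm statement with no comparator, and a perceived-change score can be tested against its midpoint. What stands is that such a test is weak and does not address improvement in level. A missing comparison arm limits attribution to the programme; it is not what breaks the hypothesis.

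**Only two items are shown.** They are offered as examples of five, the form is not final, and the REACH item combines past learning with present use. It would be wrong to say that all five are worded as change. The purpose sentence, however, covers the whole questionnaire and makes perceived change its target.

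**The lack of a T0 value is inferred.** Section 2.11.4 does not rule out a baseline, and Section 2.7 could nominally include one. This is fair, and the absence should be stated as an inference. It does not help, because items of the kind shown have no meaningful value at T0.

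**The outcome is ancillary.** It is neither primary nor secondary. The benefit of adding caregivers is tested by hypotheses 3 and 4 on the participants' own outcomes, in a randomised comparison. No mediation analysis is promised, so the trial should not be faulted for leaving a mechanism unproven. This stands and limits the seriousness of the point.

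**It might be left to an analysis plan.** This does not stand. The article itself fixes the hypothesis, the arm, the purpose of the measure and the sample wording, and no analysis can recover a starting level that the instrument does not collect.

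**Conclusion.** The point holds in this form: the caregiver questionnaire as described cannot show the enhancement that hypothesis 5 claims, because it targets perceived change after the course and its example items can give no meaningful T0 level. Agreement at T1 or T2 would describe what caregivers believe happened to them, and it is open to acquiescence.

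The effect is confined to one of five hypotheses. The primary outcome, the secondary outcome and hypotheses 1 to 4 are untouched. The figures of 20–23%, 40–46% and 81–87% for shifts of 0.2, 0.3 and 0.5 SD illustrate the vulnerability. They rest on assumed shifts, 34 to 40 respondents and a midpoint test that the protocol does not specify, and they do not estimate the bias in this trial.

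The conclusion also rests on reading the stated purpose of the questionnaire as governing the three items not shown. It should be revisited if those items turn out to be present-state statements given at T0.

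**What to change.** 1. **Reword.** Write the belief, perception and skill items as statements about the present that any caregiver can answer at any time, for example *I tell my child my reasons when I disagree with a plan*. Keep the item that names REACH as post-course feedback only, outside the test of hypothesis 5.
2. **Measure at T0, T1 and T2** in SD-PLUS caregivers, say so in Sections 2.7 and 2.11.4, and test hypothesis 5 as change from T0. The form is still to be developed, so rewording costs little. The added T0 wave is at most about 40 short forms.
3. **Where feasible, extend to the other arms.** Give the same form to caregivers already recruited and randomised in the SD and leisure arms, and estimate the T0-adjusted difference, so that any gain can be attributed to the programme. The cost is modest but real: up to 80 further people × 3 waves = 240 administrations, among caregivers with no intervention contact and in a study that reports budget limits (Sections 2.4.2 and 2.9.3). This step is desirable; hypothesis 5 as worded does not require it.
4. **If no T0 measure is added,** restate hypothesis 5 as a description of perceived change in SD-PLUS caregivers and draw no conclusion of enhancement from it. This needs no new data.

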### 2.12. Statistical Analysis

Analyses of the outcomes will be performed using the intention-to-treat principle; this method is used to avoid the effects of crossover and drop-out in clinical research. Parameters for those who withdraw will be treated using maximum likelihood estimation (i.e., the full information maximum likelihood method). This method produces approximately unbiased results across a variety of parameter estimates, particularly with a small sample size [69]. Prior to all hypotheses testing, this study will conduct a Chi-square test and a *t* test to assess whether or not the sociodemographic characteristics and the baseline conditions of the participants with ID are different among the groups. Analyses of treatment outcomes will be conducted using hierarchical linear modelling (HLM), which is suggested to have more flexible data requirements (dealing with the missing data), and stresses individual change over group differences. Moreover, the HLM analysis is able to identify differences between conditions through the presence of a significant time x treatment interaction term. To examine the magnitude of change in the three groups at post-test and follow-up, effect size statistics will be calculated using Cohen’s d [70]. Finally, regression analyses will be performed to examine the relationships between changes in self-determination competencies and personal well-being among the participants with ID.

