## 2. Materials and Methods

### 2.1. Study Design, Aims and Hypotheses

This study is a randomized controlled trial (RCT), where adult participants with mild ID and their caregivers are randomized into three arms: (1) self-determination enhancement group (SD group), (2) self-determination enhancement PLUS group (SD-PLUS group) and (3) leisure activity group (comparison group, hereafter called leisure group). SD-PLUS is the only group to include caregivers during the intervention. There will be three assessment points: pre-test (T0), post-test (T1) and follow-up (3 months later) (T2); see Figure 2 for a diagrammatic representation of the study’s design structure. To ensure equity of access to a potentially effective intervention, participants in the leisure group will receive the same SD group intervention following completion of all the assessments for the intervention arm. The study protocol was approved by The Survey and Behavioral Research Ethics Committee of The Chinese University of Hong Kong (reference no.: SBRE-18-234) and the trial was registered in the ClinicalTrials.gov Protocol Registration (registration no.: NCT05167929).

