### 2.3. Sample Size

The sample size is calculated based on a moderate effect size of 0.70 for clinical outcome research. For 80% power, an α error of 0.05, and a test including three independent groups, the required sample size is 105 participants, which is sufficient to conduct Hierarchical Linear Modelling (HLM). Incorporating an estimated drop-out rate of 15% at the six-month follow-up period, the target sample size is 120. Drop-out cases will include participants with ID whose attendance rate in regard to the groups is less than 70%, or those who cannot complete all questionnaires during the three phases. With 6–8 participants per group, 5 SD groups, 5 SD-PLUS groups and 5 leisure groups will be conducted.

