### 2.7. Data Collection Schedule

Demographic characteristics and baseline data about the participants will be collected before the group intervention commences (T0). Within one month following the completion of the intervention (T1), participants will be invited to complete the same scales used to collect baseline data (see Section 2.11) to measure any immediate effects. Three months after completion of the intervention, the same study cohort will be invited to complete the scales (T2), so as to measure the sustained intervention effects (see Figure 2). Participants of the SD groups and SD-PLUS groups will also be invited to complete the Self-Determination Action Plan at the end of the intervention. To ensure data quality, the individual face-to-face interviews will be conducted by interviewers who are trained in interviewing skills for people with ID.

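### Baseline is compared across arms by significance tests, while the outcome model states no T0 adjustment; adding one would cut the variance of every arm contrast by about 10% to 35%

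*Protocol article*

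**What the plan says.** Section 2.12 (Statistical Analysis) of the protocol article opens its testing sequence with baseline comparisons: "Prior to all hypotheses testing, this study will conduct a Chi-square test" together with a t test, "to assess whether or not the sociodemographic characteristics and the baseline conditions of the participants with ID are different among the groups". It does not say what will be done with the results.

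The same section bases the treatment comparison on hierarchical linear modelling with full information maximum likelihood. Differences between conditions are to be identified by a significant interaction of time with treatment, and the method is commended for its focus on individual change. Neither T0 as a covariate nor a common T0 mean across arms is mentioned; neither is ruled out.

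Three other places bear on the point:

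- Section 2.1 defines three randomised arms, assessed at T0, T1 and T2.
- Section 2.3 sizes the trial: "The sample size is calculated based on a moderate effect size of 0.70 for clinical outcome research", and "For 80% power, an α error of 0.05, and a test including three independent groups, the required sample size is 105 participants". The target after drop-out is 120.
- Section 2.7 fixes T0 only relative to treatment: "baseline data about the participants will be collected before the group intervention commences (T0"). Section 2.6 has the allocation passed to the NGO social workers, who then secure consent.

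**The concern.** There are two linked problems in how the T0 data are used.

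First, if allocation is sound, any difference between randomised arms at baseline is due to chance, and a p-value for it says nothing about the treatment effect. Placed ahead of the hypothesis tests and with no stated consequence, such tests invite adjustment chosen after seeing the data. The named t test also does not fit three arms.

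Second, an interaction model that treats T0 as one more outcome occasion, with its own mean in each arm, subtracts the full chance difference at T0 from the difference at T1. Baseline adjustment subtracts only the part that the T0–T1 correlation supports. The first approach is never the more precise of the two, and at a low correlation it is worse than ignoring T0 altogether. The trial would then lose precision that data it already collects could supply.

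**Working it through.** **Inputs.** From Section 2.3: effect size 0.70 (read as a standardised difference between two arms, since the metric is not named), 80% power, alpha 0.05 (taken as two-sided), 105 evaluable, hence 35 per arm if allocation is equal. From Section 2.1: three arms and three occasions. Not in the document and therefore assumed: the T0–T1 correlation rho, from 0.3 to 0.8.

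**The plan's own figure.** A two-sided two-sample t test at 0.05 with d = 0.70 needs 34 per arm for 80% power (81.2% by the noncentral t). That is 3 × 34 = 102, within 3% of the stated 105, and 102/0.85 = 120. The sample size therefore matches a comparison of two arms on one score with SD 1, without any use of T0.

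**Baseline tests.** If the t test is read as three pairwise tests on one variable, at least one p < 0.05 appears in about 12% of correctly randomised trials (simulation, 40 per arm). Treating the three tests as independent gives 1 - 0.95³ = 14.3%.

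**Variance of the T1 contrast.** In units of the outcome variance, with equal variances at T0 and T1 and complete data, each arm contributes:

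- T1 scores alone: 1
- interaction with free T0 means (difference in change): 1 + 1 - 2rho = 2(1-rho)
- T0 as covariate, or common T0 mean: 1-rho²

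The ratio of the last two is (1-rho²)/[2(1-rho)] = (1+rho)/2, so the reduction is (1-rho)/2. Generalised least squares on three occasions with equal correlations gave the same ratios: 0.65, 0.75, 0.85 and 0.90 at rho 0.3, 0.5, 0.7 and 0.8. With time as a linear slope (assumed spacing 0, 2.75 and 5.75 months) the ratios were 0.611, 0.733, 0.846 and 0.899.

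**Power at 35 per arm, d = 0.70, before clustering.** SE = √(2v/35), where v is the variance above; power = Φ(0.70/SE - 1.96). For rho = 0.5:

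- Free T0 means: v = 1.00, SE = 0.239, 0.70/0.239 - 1.96 = 0.97, power 83%.
- Adjusted: v = 0.75, SE = 0.207, 0.70/0.207 - 1.96 = 1.42, power 92%.

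| rho (assumed) | v, free T0 | v, adjusted | Variance reduction | Power, free T0 | Power, adjusted | n per arm for 80%, free → adjusted |
|---|---|---|---|---|---|---|
| 0.3 | 1.40 | 0.91 | 35% | 70% | 87% | 45 → 30 |
| 0.5 | 1.00 | 0.75 | 25% | 83% | 92% | 33 → 25 |
| 0.7 | 0.60 | 0.51 | 15% | 97% | 98% | 20 → 17 |
| 0.8 | 0.40 | 0.36 | 10% | 99.6% | 99.8% | 13 → 12 |

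These use the normal approximation; for T1 scores alone it gives 83.4%, against 82.3% by the noncentral t. Below rho = 0.5, 2(1-rho) exceeds 1, so the free-T0 contrast is less precise than T1 scores alone. Power is 76% at rho 0.4 and 70% at 0.3, under the 80% target.

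**The case against.** The strongest reply is that the article does not fix the form of the model. It gives no time coding, random effects or covariates, and a model with a common T0 mean also tests treatment through time-by-treatment terms. A condensed article may leave such detail to an analysis plan that is not shown. This stands to the extent that the loss is conditional: it arises only if the interaction is fitted with free arm means at T0. That is its usual form, and the article's stress on individual change points the same way.

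It can also be said that the baseline tests have no stated consequence and so bias no estimate, and that in condensed prose a t test may mean pairwise tests. Both are fair. The wording of the t test is a minor matter.

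Two stronger readings are tempting but not supported:

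- A reader might infer that T0 is used only for significance tests and not in the model. The interaction spans T0, T1 and T2, so T0 very probably enters as the first occasion. What is not stated is an efficient use of it.
- A reader might infer that the loss falls specially on SD-PLUS versus SD. The variance ratio is the same for every pair of arms. A smaller true difference there would make precision matter more, but the article plans no separate effect for that contrast.

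Finally, because consent and T0 may both follow allocation, arms could differ at T0 for reasons other than chance. That weakens the claim that a baseline comparison is meaningless in this trial and counts against imposing a common T0 mean. It does not make a p-value a useful basis for the treatment analysis.

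**Conclusion.** The point holds as an improvement at almost no cost, not as an error that undermines the trial. The planned baseline tests do not serve the treatment comparison, and the stated outcome analysis leaves out an adjustment that uses data already collected.

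The gain depends on rho. It is material at 0.3 to 0.5, where it can decide whether the planned effect is detected with 80% power, and small at 0.7 to 0.8, where the planned analysis already has ample power before clustering. The figures assume an interaction with free T0 means, equal variances, complete data, 35 per arm and no clustering by intervention group. The same formula applies at T2, with the T0–T2 correlation in place of rho.

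**What to change.** In Section 2.12:

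1. Replace the chi-square and t tests of baseline with a descriptive table by arm, without p-values.
2. State that the hierarchical model takes T1 and T2 as outcomes with the T0 score of the same scale as a covariate, and reports the arm contrasts at each time.

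Both are changes of wording and need no new data.

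A model with a common T0 mean across arms is an alternative only if T0 is measured before the allocation is known. Sections 2.6 and 2.7 do not guarantee this. Moving T0 ahead of allocation would change trial conduct, and its cost should be judged separately. T0 as a covariate does not impose equal arm means, so it can be adopted without that move, although no form of the model repairs T0 scores already shifted by knowledge of the arm.
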